## Abstract

**Background:**

There is significant variability in clinical pathways available in the diagnostic assessment of ASD, including the order and timing of allied health assessments in relation to paediatrician consultations. Allied health professionals in first-contact models are increasingly used to improve the timeliness of healthcare access, whilst complementing medical specialty workforce shortages. Anecdotally, the implementation of allied health first-contact models in paediatrics has improved waitlists and timely access to healthcare. However, no rigorous studies have been conducted to evaluate the outcomes of these models. This study aims to determine the impacts of an allied health first-contact model on health service use and costs and patient quality of life and satisfaction.

**Methods:**

An open, semi-blinded, multi-centre randomised controlled trial in paediatric outpatient clinics at two Australian metropolitan public hospitals. 56 children (0–16 years) fulfilling the inclusion criteria will be randomised to one of two clinical pathways for assessment of ASD: (1) allied health first-contact or (2) medical first-contact model. Cost outcomes will be collected from both health service and family perspectives. Caregiver-reported outcome measures include: Pediatric Quality of Life Inventory (PedsQL), the EuroQOL Five Dimension Youth Version (EQ-5D-Y), the Autism Family Experience Questionnaire (AFEQ) and Measure of Processes of Care.

**Discussion:**

Evidence of improvements in service and consumer centric outcomes will help inform the development and implementation of high-value, evidenced based models of care for the assessment of ASD in children. The findings from this study are expected to contribute to the evidence base around the costs and consequences of allied health first contact models for the assessment of children with ASD in the Australian setting. Findings of this study may help to inform the allocation of health care resources while maintaining, or potentially improving, patient and family quality of life and experience of care. These findings may be useful in informing the wider adoption of these models in Australia and internationally, particularly in healthcare settings where medical specialist shortages exist.

**Trial registration:**

Australia and New Zealand Clinical Trials Register (ANZCTR) ACTRN12621001433897. Registered: 25^th^ October, 2021.

## Background

Autism Spectrum Disorder (ASD) is a neurodevelopmental disorder which is characterized by social-communication impairment and by repetitive patterns of behavior [1]. In Australia, the prevalence of ASD in children is estimated between 2.4% to 3.9% [2]. Early diagnosis of ASD is considered best practice as early intervention for emotional regulation, communication, cognitive, behaviours, physical, sensory processing and/or social skills support provides children with improved educational outcomes and quality of life [3, 4]. The Australian Guidelines for ASD assessment acknowledge the importance of allied health (e.g. psychologist, speech pathologist, occupational therapist) contributions to the clinical diagnosis of ASD within a multidisciplinary team setting [5]. However, in clinical practice there is significant variability in clinical pathways available in the diagnostic assessment of ASD, including the order and timing of allied health assessments in relation to paediatrician consultations.

Allied health professionals in first-contact models are increasingly used to improve the timeliness of healthcare access, whilst complementing medical specialty workforce shortages [6, 7]. Dietitian and Speech Pathology/Audiology first-contact models have been effective in reducing medical specialty waitlists in adult populations [8–10]. A recent Australian study demonstrated that dietitian first-contact models in the management of low-risk gastroenterology conditions resulted in high consumer satisfaction with services and improved quality of life outcomes [8, 9]. This is important in the sustainable delivery of patient-centric, high value healthcare [11].

Within the paediatric population in Queensland, Australia, multidisciplinary allied health first-contact models of care for the assessment of ASD exist across several healthcare facilities [12]. In this model, children are first seen by a psychologist, speech pathologist, occupational therapist and/or social worker before initial contact with a medical specialist (e.g. Paediatrician). Anecdotally, the implementation of allied health first-contact models in paediatrics has improved waitlists and timely access to healthcare. However, no rigorous studies have been conducted to evaluate the outcomes of these models, when compared with traditional medical first-contact models of care. This is a critical gap in the literature as service and consumer centric outcomes are needed to inform the development and implementation of high value, evidence based models of care in the diagnostic assessment of ASD in children. In this study, we will conduct a randomised controlled trial to determine the impacts of an allied health first-contact model on health service use and costs and patient quality of life and satisfaction.

## Methods

### Aims

This aim of this study is to determine if an allied health first-contact model of care reduces health service use and costs without compromising patient quality of life or satisfaction when compared to traditional medical first-contact models of care in the assessment of ASD in children. We hypothesize that an allied health first-contact model of care reduces healthcare use and costs; and results in comparable patient quality of life and satisfaction with care, when compared to a traditional medical first-contact model of care.

### Study design

This trial is designed as an open, semi-blinded, randomised controlled trial within paediatric outpatient clinics located at secondary Australian public hospitals: Caboolture Hospital and The Prince Charles Hospital (TPCH).

### Participants

Children who have been referred to a Paediatrician for assessment of suspected ASD will be eligible to participate in the study. Additionally, enrolled children will meet the following inclusion criteria: aged between 0 to 16 years; referral for a cognitive, behavioural, learning and/or developmental assessment and determination by the triaging team that the assessment of ASD is warranted as part of the differential diagnosis process. Children will be excluded from participation in the study if they have received two or more allied health assessments completed in past 12 months, children in out of home care, a previous diagnosis of ASD and/or acute functional deterioration requiring urgent medical review.

### Recruitment

All referrals will be screened for eligibility by a member of the research team. Informed consent will be obtained and caregivers will be provided with a caregiver information sheet and study brochure. The researcher will verbally go through the caregiver information sheet, study brochure and consent form for all caregivers of eligible participants. Interpreter services may be utilized to assist with obtaining informed consent when caregivers are identified with non-English speaking backgrounds.

It is possible that some caregivers will identify as having literacy issues. In such instances, additional time will be allocated to explain the study and obtain informed consent [13]. The additional time used to obtain informed consent will include the “teach back” method to ensure that the caregivers understand the risks and processes involved in participating in the study [14].

### Randomisation

An independent biostatistician will generate a randomisation list, which will include block size permutations of *n* = 5 to ensure an equal number of participants enrolled in each group and to minimise selection and accidental bias [15]. Model of care allocation (allied health versus medical first pathway) will be assigned by a clinic nurse independent of the research team following enrolment. The opening of concealed sequentially numbered opaque envelopes which contain the group allocation will only be completed by the clinic nurses at each site.

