### Statistical analyses

To account for clustering at the hospital level and repeated measures over time, multivariable mixed-effects regression models will be built to estimate the interventional effect of health related quality of life and patient experiences between and within groups. Multivariable mixed-effects regression models were chosen to to minimise bias due to group imbalance and its effects on the internal validity of the study [23]. For each model building process, variables found to be significantly associated with the outcome measure in the univariable analysis at the 10% level will be retained in the final model. As the primary predictor of interest, intervention effect will be forced into the multivariable model. Continuous outcome measures will be analysed using linear regression models. For dichotomous measures, the analysis will be by binary logistic regression, while multinomial logistic regression will be used to analyse nominal measures. Model diagnostics will be conducted on all models to ascertain their appropriateness. Each model will be tested for violations of model assumptions, the existence of influential points and goodness of fit. Tests for all outcomes will be two-tailed, with levels of statistical significance set at 5%. To assess the missingness mechanism, Little’s test for missing completely at random (MCAR) will be used.

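### Blocks of 5 in a two-arm trial do not ensure the equal group sizes they are said to ensure

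*Protocol article*

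**What the plan says.** All references are to the protocol article.

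- **Randomisation.** An independent biostatistician prepares the list in permuted blocks. The size is given, with its purpose, as "5 to ensure an equal number of participants enrolled in each group and to minimise selection and accidental bias". No other block size appears in the article.
- **Randomisation.** There are two arms: "Model of care allocation (allied health versus medical first pathway) will be assigned by a clinic nurse" who is independent of the research team. Opening the sequentially numbered opaque envelopes "will only be completed by the clinic nurses at each site".
- **Abstract, Methods.** "56 children (0–16 years) fulfilling the inclusion criteria will be randomised to one of two clinical pathways".
- **Sample size and statistical power.** The requirement is 26 per group, which is 52 in total and presumes equal arms.

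**The concern.** The sentence gives a number and a purpose, and the two conflict. Permuted blocks keep two arms equal only if each block can be halved, and 5 cannot. This differs from a detail left to a fuller document: the article chose to state the block size and the property it secures, and the stated size does not secure it.

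What is at stake is mainly the correctness of a core item of trial conduct. Someone generating or auditing the list from this sentence could not tell what to produce. They would have to decide which arm takes the third place in each block, and the text gives no rule for that. A systematic choice would push the trial towards 3:2 allocation, which nobody intended. Power is a secondary matter and, as shown below, a small one.

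**Working it through.** **Inputs.** Two arms, equal numbers intended, block size 5 (Randomisation); N = 56 (Abstract); N = 2 × 26 = 52 (Sample size and statistical power). The article does not say how the majority arm of a block is chosen, so two assumptions are taken: at random for each block, or always the same arm.

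**The plan's own figure.** The 26 per group cannot be confirmed from the stated inputs, because the mean number of appointments is not given. If means of 2 and 1 are assumed for Poisson counts, with two-sided 5% and 80% power, the square-root formula gives 7.849 / [2(√2 − 1)²] = 22.87, rounded to 23. Then 23 / 0.9 = 25.6, or 26. This formula takes equal arms.

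**Parity.** 5 / 2 = 2.5, so a completed block is 3:2 or 2:3, a difference of ±1. Also 52 / 5 = 10.4 and 56 / 5 = 11.2, so the last block is incomplete at either total.

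**Majority arm random, N = 56.** Eleven complete blocks give eleven independent ±1 terms, and the one remaining child adds another. The arm difference d is a sum of twelve ±1 terms.
- P(d = 0) = C(12,6) / 2¹² = 924 / 4096 = 22.6%.
- P(|d| ≥ 4) = 1 − (924 + 2 × 792) / 4096 = 1588 / 4096 = 38.8%.

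**Majority arm random, N = 52.** Ten complete blocks give S, a sum of ten ±1 terms. The first two places of the last block add +2, 0 or −2 with probabilities 0.2, 0.6 and 0.2.
- P(d = 0) = [0.6 × 252 + 0.2 × 210 + 0.2 × 210] / 1024 = 235.2 / 1024 = 23.0%.
- P(d = 2) = [0.6 × 210 + 0.2 × 252 + 0.2 × 120] / 1024 = 200.4 / 1024 = 19.6%, and the same for d = −2.
- P(|d| ≥ 4) = 1 − (235.2 + 2 × 200.4) / 1024 = 37.9%.

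A simulation of 200,000 lists agrees: 22.5% equal and 38.8% differing by 4 or more at N = 56; 23.0% and 37.8% at N = 52. The mean absolute difference is about 2.7 at both totals.

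**Same arm always favoured.**
- N = 56: 33:22 after eleven blocks, ending 33:23 or 34:22, expected difference 11.2.
- N = 52: 30:20 after ten blocks, most often ending 31:21, expected difference 10.4.

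**Efficiency relative to equal arms:** 4n₁n₂ / N² = 1 − (d / N)².

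| Case | Efficiency | Loss |
|---|---|---|
| Random majority, N = 56, E(d²) = 12 | 1 − 12/3136 | 0.4% |
| Random majority, N = 52, E(d²) = 10 + 1.6 = 11.6 | 1 − 11.6/2704 | 0.4% |
| 30:26 | 3120/3136 = 0.995 | 0.5% |
| 31:21 | 2604/2704 = 0.963 | 3.7% |
| 34:22 | 2992/3136 = 0.954 | 4.6% |

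**After the change.** With blocks of 4 on a single list, 52 / 4 = 13 complete blocks (26:26) and 56 / 4 = 14 complete blocks (28:28).

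**The case against.** The best defence is that the wording is loose rather than the list wrong. The phrase might mean five per arm, so blocks of 10, or five different block sizes. Either could be a sound scheme. But the article says neither, and the literal reading is the only one its words give. Even five per arm would not guarantee equality on a single list: 52 leaves two places in the last block (difference up to 2), and 56 leaves six (up to 4). So the sentence needs correction on any reading.

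It is also fair to say that little harm follows. Unequal numbers that arise from concealed random allocation do not bias the comparison, and the usual loss of efficiency is under 1%. That stands, and it limits the severity.

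A reader might infer more than the article supports:

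- *That blocks of 5 cannot give equal arms at all.* This is true of each completed block but not of the total, which is equal by chance in more than a fifth of lists. What fails is the guarantee.
- *That randomisation is unstratified by hospital.* The article is silent on this. Envelopes opened by nurses at each site are compatible with separate site lists, and a condensed article may leave this to the full protocol.
- *That the analysis is stratified by hospital, so the design does not match it.* The Statistical analyses section says "To account for clustering at the hospital level and repeated measures over time" it will use mixed-effects models, for quality of life and patient experience. That is not a stratified analysis.
- *That allocations become guessable.* Nothing says site staff know the block size. Envelopes are opaque and opened after enrolment by nurses independent of the research team. An odd size is not what helps guessing either: with a random majority arm, the last place in a block of 5 stays open after a 2:2 start, whereas the last place in a block of 4 is always determined.
- *That arm will be partly aligned with hospital and visit counts will differ by site.* The article gives no figures by hospital.

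**Conclusion.** Wrong as written; severity minor to moderate. The stated block size contradicts the stated purpose, and nothing else in the article corrects it. The parity result needs no assumption beyond two arms and the literal reading of 5. The percentages of equal and unequal lists rest on a random majority arm in each block and on a single list of 52 or 56. The loss of about 4–5% rests on every block favouring the same arm, which the article does not say and which should be read as the unfavourable end. The point does not put the validity of the comparison in doubt.

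**What to change.** Replace the block size in the Randomisation section with one or more even sizes compatible with 1:1 allocation, for example: *randomly permuted blocks of size 4, allocation ratio 1:1*. Randomly varied even sizes also serve. In that case the claim should be that group sizes are kept close, because an incomplete last block can leave a small difference. The same applies if each hospital has its own list: with blocks of 4, each site's incomplete last block can leave a difference of at most 2.

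If n = 5 meant five per arm or five different block sizes, correct the sentence to say that and list the sizes. If blocks of 5 were actually used, regenerate the list and the unopened envelopes; children already allocated keep their allocation.

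The cost is one sentence and, at most, a new list and a new set of envelopes. No extra participants or staff are needed. Under the article's Ethics approval section, a protocol change also needs ethics committee approval and, if judged major, a registry update.

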### Blinding

Blinding will be maintained by emphasising to intervention staff and participants that each model of care adheres to best practice principles, and each is advocated by certain professionals to be superior for the assessment of ASD in children. Except for the interventionists (i.e. paediatricians and allied health staff) and clinic nurse, study investigators and staff will be blinded to group allocation of the participants. The trial will adhere to established procedures to maintain separation between the study research assistant that takes outcome measurements and the healthcare staff that deliver the intervention. The research assistant will obtain all outcome measurements and will not be informed of the group assignment. All investigators, staff, and participants will be kept masked to outcome measurements and trial results until the conclusion of the study.

### Outcome measures

Cost outcomes will be estimated from both health service and family perspectives. Health service use and costs will include all allied health and specialist outpatient appointment costs, as well as the length of stay and cost of any hospital admissions. Family costs will include costs associated with travel to appointments, including parking costs, and time off work to attend appointments.

Caregiver-reported outcome measures will be collected using the following validated questionnaires: Pediatric Quality of Life Inventory (PedsQL) [16] child module (Score 0 to 100; parent or child completed), the EuroQOL Five Dimension Youth Version (EQ-5D-Y) [17], the Autism Family Experience Questionnaire (AFEQ) [18] and Measure of Processes of Care [19]. Patient wait times to access care will also be recorded.

### Data collection

Figure 1 provides an outline of the RCT. At enrollment, the research assistant will collect baseline demographics data and complete the Peds-QL and EQ-5D-YL with the child and/or caregiver via a face to face meeting or phone review, whichever method is preferred by the caregiver. As the EQ-5D-Y questionnaire is designed for completion by children aged 8–15, we will attempt to obtain both child and parent-proxy completed measures for children in this age bracket.

**Fig. 1 Fig1:**
[figure not shown]
OT = Occupational Therapist; SP = Speech Pathologist; SW = Social Worker; Psych = Psychologist; PedsQL = Pediatric Quality of Life; GP = General Practitioner; ASD = Autism Spectrum Disorder; EQ-5D-Y: EuroQOL Five Dimension Youth Version

At the first allied health or medical specialist appointment, the research assistant or clinician will meet the caregiver in the waiting area and provide them with a cost diary to complete. Cost diaries will be used to record all travel-related costs as well as the number of hours of caregiver time off work required to attend appointments. For subsequent allied health or medical specialist appointments, the research assistant will obtain cost diaries from the caregiver either on the day or up to 48 h post their child’s appointment at the hospital. Collection of completed cost diaries will be from any of the following modalities, whichever is preferred by the caregiver: face to face, phone review, or email.

The Research Assistant will also complete the Peds-QL, EQ-5D-YL, The Autism Family Experience Questionnaire (AFEQ) and Measure of Processes of Care with the child and/or caregiver either on the day or up to 7 days post their child’s last medical specialist appointment at the hospital. Collection of surveys will be either face to face or in a phone review, whichever is preferred by the caregiver.

For phone reviews, a reminder text message will be sent prior to the scheduled review to remind the caregiver of the scheduled date and time. A reminder text message is planned for this trial to allow caregivers the opportunity to reschedule, if a more appropriate time/date is desired. Additionally, a reminder text message is anticipated to assist with retention of participants over the trial period. Similar to previous trials conducted by the research team, a total number of three communication (e.g. text, phone, letter) attempts is allowed at any review time point [20].

### Study completion

Once all participants have reached the end of the trial period, the study investigators will request a retrospective data extraction of allied health and specialist outpatient appointment dates and costs, as well as any emergency hospital presentations and hospital admissions dates and costs, for all participants. These data are routinely collected within heath service databases.

### Safety considerations/patient safety

The research team will adhere to the principles of the Declaration of Helsinki [21] and Good Clinical Practice when conducting this study [21]. Only the study investigators affiliated with Queensland Health will have access to identifiable information, as per our ethically approved study protocol. De-identified information will only be seen by investigators on the study. Identifiable study information will be securely stored on a database within Queensland Health computer systems. All original clinical record forms will be in a locked cabinet at Caboolture Hospital, in accordance with National Health and Medical Research Council (NHMRC) guidelines and Australian regulations (e.g. minimum 15 years after the child reaches the age of 18).

### Sample size and statistical power

Accepting an alpha risk of < 0.05, a beta risk of < 0.2 and assuming a 10% risk of dropout during follow-up, *n* = 26 patients in each group is required to identify a statistically significant reduction of at least one medical appointment between groups. The sample size determination was not reliant on the standard deviation as a sample size formula input due to the number of medical appointments being considered a count variable [22].

### Statistical analyses

To account for clustering at the hospital level and repeated measures over time, multivariable mixed-effects regression models will be built to estimate the interventional effect of health related quality of life and patient experiences between and within groups. Multivariable mixed-effects regression models were chosen to to minimise bias due to group imbalance and its effects on the internal validity of the study [23]. For each model building process, variables found to be significantly associated with the outcome measure in the univariable analysis at the 10% level will be retained in the final model. As the primary predictor of interest, intervention effect will be forced into the multivariable model. Continuous outcome measures will be analysed using linear regression models. For dichotomous measures, the analysis will be by binary logistic regression, while multinomial logistic regression will be used to analyse nominal measures. Model diagnostics will be conducted on all models to ascertain their appropriateness. Each model will be tested for violations of model assumptions, the existence of influential points and goodness of fit. Tests for all outcomes will be two-tailed, with levels of statistical significance set at 5%. To assess the missingness mechanism, Little’s test for missing completely at random (MCAR) will be used.

An economic evaluation will take the form of a cost-consequence analysis, where descriptive statistics including means, standard deviations and 95% confidence intervals will be used to summarise differences across all relevant cost and outcome measures between the two models of care. This type of economic evaluation design was chosen to reflect the nature of the intervention where improvements are expected to be seen across a range of health service and patient outcomes (including family out of pocket costs, health system costs, quality of life, patient experience, patient satisfaction, wait times). The cost-consequence analysis framework allows for any changes in these outcomes to be reported clearly and transparently without the restriction of needing to identify a single outcome measure of interest, as is the case with cost-effectiveness analysis. The reader or decision maker is then able to form an opinion about the value of this service change taking account of all relevant costs and outcomes. Specific cost categories to be reported on in the analysis will include allied health and specialist outpatient appointment costs, emergency department presentations, hospital admissions costs and costs of patient (family) travel and time off work to attend appointments. EQ-5D-Y responses will be converted to a utility score using an appropriate published value set. Utility scores will be reported separately for child self-completion and caregiver proxy completion questionnaires. These utility scores will then be used to generate estimates of Quality Adjusted Life Years (QALYs) for each treatment group.

As this study is registered on the ANZCTR and occurring within Metro North Hospital and Health Service, the trial may be randomly audited by an independent study monitor at any time point in the study. Given that this study is unblinded and not comparing rates of mortality or major morbidity, a data monitoring committee will not be set up for the purposes of this specific study.

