The methodological and practical challenges of measuring and valuing quality of life in paediatric cohorts are well recognised, [24–26] and the evidence base continues to evolve in this field [27]. Additional challenges are present when children have mental disorders that may impact on cognition, literacy or other factors relating to their ability to respond to a questionnaire. Arguments have been made for the merits and limitations of both child-reported and parent proxy-reported completion. In this study, we will adhere to current guidance suggesting that both types should be collected simultaneously where possible [28]. Nevertheless, future studies could consider the incorporation of clinical outcomes (e.g. cognition, speech and language) in conjunction with caregiver-reported outcomes to strengthen the rationale for healthcare professionals to adopt specific service models in the assessment of ASD in children.

The findings from this study are expected to contribute to the evidence base around the costs and consequences of allied health first contact models for the assessment of children with ASD in the Australian setting. If the study hypotheses prove to be correct, this model may free up scarce health care resources while maintaining, or potentially improving, patient and family quality of life and experience of care. These findings may be useful in informing the wider adoption of these models in Australia and internationally, particularly in healthcare settings where medical specialist shortages exist.

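### The analysis section counts before-after change within one arm as an intervention effect on quality of life; only the contrast between arms is one

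*Protocol article*

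**What the plan says.** The Statistical analyses section of the protocol article builds multivariable mixed-effects models to "estimate the interventional effect of health related quality of life and patient experiences between and within groups". The same paragraph adds "As the primary predictor of interest, intervention effect will be forced into the multivariable model", and then "Tests for all outcomes will be two-tailed, with levels of statistical significance set at 5" per cent. It does not say whether that testing rule covers within-group changes.

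Under Data collection, PedsQL and EQ-5D-Y are completed at enrolment and again on the day of the last medical specialist appointment or up to 7 days later. The text places the Autism Family Experience Questionnaire and the Measure of Processes of Care only at that second time. A within-group change can therefore be formed for PedsQL and EQ-5D-Y but not for the experience measures, and this point concerns only the first two.

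The purpose is comparative. The Aims section asks whether the new model reduces use and costs "without compromising patient quality of life or satisfaction when compared to traditional medical first-contact models of care", and hypothesises that it "results in comparable patient quality of life and satisfaction with care, when compared to a traditional medical first-contact model of care". The economic analysis will "summarise differences across all relevant cost and outcome measures between the two models of care". The Discussion says that, if the hypotheses are correct, "this model may free up scarce health care resources while maintaining, or potentially improving, patient and family quality of life and experience of care".

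**The concern.** Randomisation protects the comparison between arms. It does not protect the comparison of a child's score at the end with the same child's score at enrolment. Between those two times the child grows older, waits, is assessed, and may drift back towards a usual level after being referred at a bad moment. All of this enters the within-arm change, and it would be there whichever professional saw the child first. The second measurement is also tied to the last specialist appointment and not to a fixed date, so elapsed time varies between children and may vary between arms.

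The sentence does not offer within-group change as description. It puts it under the same label as the between-arm contrast, as an estimate of the effect of the intervention. An author who followed the text could report a rise from baseline in the allied health arm as an effect of the pathway. Two conclusions would then be wrong: that quality of life improved because of the new pathway when the arms do not differ, and that it was maintained or improved when the new arm did worse than control.

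**Working it through.** **The passages side by side.** The analysis sentence names two targets, between and within groups, and calls both the intervention effect. The forced intervention term, the aim, the hypothesis and the economic summary all refer to the contrast between the two models of care. The within-group target has no counterpart in the aims.

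**What each quantity estimates.** Let the mean change from enrolment be T + A in the allied health arm and T + M in the medical arm. T is what happens to such children over the period in any case; A and M are the contributions of the pathways. The within-arm change estimates T + A. The between-arm contrast estimates A − M, because T cancels (given comparable timing of follow-up). The question in the Aims section concerns A − M.

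**Illustration of size.** The article gives no figure on this point to reproduce, and no standard deviation or expected change for PedsQL or EQ-5D-Y. The changes below are therefore assumptions, in units of the SD of the change score.

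Inputs:
- 26 per group and 10% dropout (Sample size and statistical power): 26 × 0.9 = 23.4, taken as 23 completers per arm.
- Two-sided 5% tests (Statistical analyses).
- Assumed: normal change scores with SD 1; a paired t-test within the allied health arm and a two-sample t-test between arms, as simple stand-ins for the corresponding model contrasts.

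Formulas: the within-arm statistic follows a non-central t with n − 1 = 22 degrees of freedom and non-centrality d√n. The between-arm statistic has 2n − 2 = 44 degrees of freedom and non-centrality δ√(n/2), where δ is the difference between arms.

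*The same true improvement d in both arms, so no pathway effect (δ = 0):*

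| d (SD) | d√23 | Significant rise within allied health arm | Between-arm test favours allied health |
|---|---|---|---|
| 0.2 | 0.96 | 15% | 2.5% |
| 0.3 | 1.44 | 28% | 2.5% |
| 0.5 | 2.40 | 63% | 2.5% |
| 0.8 | 3.84 | 96% | 2.5% |

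A simulation of 50,000 trials per row gave the same values to within rounding. With 26 completers per arm the entries for 0.3 and 0.5 SD are 31% and 69%, so the number of completers matters little.

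*Allied health arm truly worse by 0.5 SD (improvement 0.5 against 1.0):* the within-arm test still shows a significant rise in 63% of trials, since it depends only on d = 0.5. The between-arm test never favoured the new arm in the simulation and detected the deficit in 38% (δ√(n/2) = 0.5 × √11.5 = 1.70).

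**The case against.** The strongest reply is that this is a loose label and not a faulty analysis. The between-arm effect is estimated, named as the primary predictor and kept in every model. The hypothesis and the economic summary are comparative. A repeated-measures model naturally yields both kinds of estimate, and reporting both is common. Most of this stands, and it limits the point to the wording of what is estimated. It does not remove the point, because the sentence does attach the intervention effect to the within-group quantity, and an analysis plan that followed it would carry that forward.

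Three stronger readings are tempting, and the documents do not support them.

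- A reader might infer that the trial will judge quality of life as maintained or improved from a P value within one arm, or by noting significance in one arm and not the other. The article sets no such rule. The Discussion wording, "maintaining, or potentially improving, patient and family quality of life and experience of care", names no comparator itself, but its sentence is conditional on the study hypotheses, which are comparative. Error rates for a rule of significance in exactly one arm would describe a procedure that the plan does not contain.
- A reader might infer that calling quality of life maintained is wrong whenever the arms do not differ. It is not: that conclusion agrees with the stated hypothesis of comparable outcomes.
- A reader might infer that removing within-arm tests cures the habit of reading non-significance as no harm. It does not. If the allied health arm declined by 0.3 SD and the control arm did not change, the between-arm test would itself be non-significant in about 83% of trials with 23 per arm and 81% with 26 (power 0.169 and 0.186). That is a matter of sample size and margin, separate from this point.

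**Conclusion.** The point holds in a limited form. The analysis section misstates what counts as the intervention effect on PedsQL and EQ-5D-Y by including change within an arm. The consequence is a risk that the wording leaves open, not a conclusion that the plan prescribes.

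On size, a shared improvement of 0.3 to 0.5 SD would give a significant within-arm rise in roughly 28% to 63% of trials with no difference between pathways. These figures rest on assumed effects, normal change scores, 23 completers per arm and simple t-tests in place of the mixed model. They show how uninformative a within-arm rise is about the pathway; they do not forecast what this trial will report. The wording should be changed, because the correction is nearly free and brings the sentence into line with the aims.

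**What to change.** In the Statistical analyses section, delete the reference to effects within groups. State that the intervention effect on PedsQL and EQ-5D-Y is the between-arm contrast, either the baseline-adjusted difference at follow-up or the arm-by-time term, reported with its 95% confidence interval. Add that within-arm mean changes are shown as description only, without P values, and are not used to support statements that quality of life was maintained, improved or not compromised.

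This takes one or two sentences and needs no extra data or participants. The downside is that significance statements about change within each arm are lost; the changes themselves can still be reported.
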